##### Blinding

The team member that prepared the randomization schedule will meet with the pre-specified unblinded study personnel prior to the site initiation visit. The unblinded personnel will then prepare sealed envelopes that contain each subject’s group assignment.

We will designate, a priori, study personnel that will be unblinded. These unblinded personnel will be directly involved with preparing the blinded medications and maintaining the drug log. The unblinded pharmacist/coordinator will access the actual treatment assignment but both blinded study personnel and the patient will not know the patient’s treatment assignment. Treatments will be prepared by designated unblinded personnel who will have no other patient contact.

Should an investigator become inadvertently unblinded, the principal investigator and medical officer will determine the extent of the unblinding and potential ramifications. If necessary, the investigator’s role may need to be altered to only include tasks affiliated with unblinded personnel. Should a patient become inadvertently unblinded, that patient’s data will continue to be collected for safety purposes; however, the data will not be used for the final analyses and a replacement subject will be enrolled. Unblinding of a subject(s) group assignment will be documented and will include an explanation of why the study medication was unblinded. Following data lock, group assignment can be unblinded and the unblinded information can be sent to the study participants at the discretion of the principal investigator.

#### Adherence

Adherence to the treatment protocol will be assessed and verified through the completion of the drug log. The drug log will be maintained by unblinded study personnel and inspected on no less than an annual basis by an unblinded study co-investigator.

Patient adherence to the medication will be documented through weekly patient self-report. The patients will be asked to take 1 pill daily during the 6-month prescription, thus 1 day will equate to 1 pill. Patients will be provided a weekly SMS text notification with a link to REDCap to ask if the patient has taken the medication that day. Previous literature has defined good medication compliance as taking at least 80% of the prescribed medication [55]. We will calculate the proportion of patients who meet this criterion in the treatment group as well as the 95% confidence interval (CI) around this compliance rate. The treatments will be considered feasible and acceptable if over 70% of participants reach this threshold.

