Breaking the randomization code will be performed by the study’s medical officer and will occur if it is necessary for the care of the subjects. For example, if an adverse event or serious adverse event occurs with a subject and knowledge of the drug randomization would be important for clinical care or to determine appropriate treatment, then the principal investigator will break the code and the subject will be withdrawn from the study. If a subject discontinues the study for any reason prior to the 6-month follow-up visit, then the collected data will be evaluated but not included in the analysis and a replacement subject will be enrolled in the study. There are no provisions for ancillary or post-trial care.

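### The 80% adherence criterion is read from one question a week about a single day, and early discontinuers may drop out of the 70% feasibility rate

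*Protocol article*

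**What the plan says.** All references are to the Protocol article.

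- **Criterion.** The Adherence section takes its per-patient standard from the literature: "Previous literature has defined good medication compliance as taking at least 80% of the prescribed medication". It fixes the unit too: "The patients will be asked to take 1 pill daily during the 6-month prescription, thus 1 day will equate to 1 pill".
- **Measurement.** In the same section, "Patient adherence to the medication will be documented through weekly patient self-report", by means of a "weekly SMS text notification with a link to REDCap to ask if the patient has taken the medication that day".
- **Second source.** The section opens with "Adherence to the treatment protocol will be assessed and verified through the completion of the drug log". Unblinded personnel keep this log, and it is inspected at least once a year. The article does not say that it records capsules taken or returned, or that the 80% figure comes from it.
- **Decision rule.** "We will calculate the proportion of patients who meet this criterion in the treatment group", with a 95% confidence interval, and then "The treatments will be considered feasible and acceptable if over 70% of participants reach this threshold". The first sentence refers to the treatment group and the second to participants, so the denominator is not settled.
- **Discontinuation.** For anyone who discontinues the study before the 6-month visit, "then the collected data will be evaluated but not included in the analysis and a replacement subject will be enrolled in the study". This stands under Study stopping rules, after the list of mood and behaviour changes, and is repeated under Randomization. Neither place makes an exception for adherence. The randomisation schedule has 40 places for 30 participants.

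**The concern.** The criterion is a fraction of all daily doses, but the question asked of patients covers one day a week. The other six days are never asked about, so no later analysis of the answers can recover them. A participant whose true adherence lies near 80% may fall on either side of the line by chance.

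The denominator is a separate matter. People who leave before month 6 have not completed the course and are the likeliest to miss the threshold. If they are removed and replaced, the rate describes those who stayed.

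At stake is a stated conclusion. Oral administration, the Discussion and its closing paragraph all present feasibility and acceptability as things this trial will assess, and the closing paragraph expects the results to inform larger trials. The Discussion itself names adherence to a 6-month course as a main challenge. With about 15 people in the arm, one or two classifications can decide the result.

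**Working it through.** **The plan's own figure.** The only design calculation is the power in the Power analysis section. A two-sample t-test with 15 per group, difference 3.09 ms, SD 2.86 ms (d = 3.09/2.86 = 1.08), 28 degrees of freedom and two-sided alpha 0.05 (assumed, as the article gives none) has power 81.49%. The stated 81.5% reproduces. No calculation is given for the 70% rule.

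**Step 1: share of doses observed.** Six months is taken as 26 weeks, or 26 × 7 = 182 capsules (assumption). Treatment starts 10 days after surgery; if the course ends 6 months after surgery, it lasts (182 − 10)/7 = 24.6 weeks. The number of weekly answers W is therefore taken as 24 to 26. With 26 answers, 26/182 = 1/7 of doses are observed.

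**Step 2: misclassification of one participant.** Assume every text is answered truthfully and days are independent with true adherence p. The participant passes if the number of yes answers X is at least r, the smallest whole number not below 0.8W: r = 20, 20 and 21 for W = 24, 25 and 26. P(pass) is the binomial tail P(X ≥ r | W, p).

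| True adherence | Error | W = 24 | W = 25 | W = 26 |
|---|---|---|---|---|
| 70% | classed as adherent | 0.111 | 0.193 | 0.163 |
| 75% | classed as adherent | 0.247 | 0.378 | 0.337 |
| 78% | classed as adherent | 0.366 | 0.518 | 0.477 |
| 82% | classed as non-adherent | 0.439 | 0.288 | 0.322 |
| 85% | classed as non-adherent | 0.287 | 0.162 | 0.185 |
| 90% | classed as non-adherent | 0.085 | 0.033 | 0.040 |

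A hypergeometric check, drawing 26 of 182 days with the true fraction fixed, gives 0.137, 0.309 and 0.470 for a false pass at 70%, 75% and 78%, so the binomial model is not driving the result.

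**Step 3: the decision rule.** Of 15, 10/15 = 66.7% fails and 11/15 = 73.3% passes. The exact (Clopper-Pearson) 95% CI for 11/15 is 44.9-92.2%. If both arms counted, the smallest pass would be 22/30 = 73.3%, CI 54.1-87.7%.

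**Step 4: restoring excluded discontinuers.** Suppose k of 15 analysed participants pass and m discontinuers in the arm were removed, all below the threshold. The rate among all starters is k/(15 + m).

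| Analysed result | m = 1 | m = 2 | m = 3 | m = 4 | m = 5 |
|---|---|---|---|---|---|
| 11/15 = 73.3% | 68.8% | 64.7% | 61.1% | 57.9% | 55.0% |
| 12/15 = 80.0% | 75.0% | 70.6% | 66.7% | 63.2% | 60.0% |
| 13/15 = 86.7% | 81.2% | 76.5% | 72.2% | 68.4% | 65.0% |

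One discontinuer reverses 11/15, three reverse 12/15 and four reverse 13/15.

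**Step 5: which m is plausible.** The Discussion cites 88% completion of a 6-month oral course in another trial. Reaching 15 completers at that rate takes 15/0.88 = 17.0 starters, so about two discontinuers per arm. Minimizing attrition expects under 10% loss: 15/0.90 = 16.7, so fewer than two. Five would use the whole spare allowance of one arm, (40 − 30)/2.

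**The case against.** The strongest reply is that this is a journal article condensing a longer protocol, and that it names a drug log as well as the text. The log may hold dispensing or return counts. That stands as far as it goes: one should not infer that no other adherence record exists. But the article assigns patient adherence to the weekly self-report, and nothing says that the log yields the 80% figure.

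Second, the exclusion is worded for those who discontinue the study, says that their data will be evaluated, and does not mention the adherence rate. Stopping treatment under the stopping rules is not stated to mean leaving the study, so people who stop capsules but keep attending may stay in the denominator. This also stands. Applying the exclusion to adherence is the natural reading of a rule without exceptions, but it is not an express statement.

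Third, a reader might infer that the text inflates the rate because it reminds participants on the day it asks about. A prompting effect would be upward, but the article gives no figure for it and no time of sending, and sampling alone also fails good adherers.

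Fourth, a reader might infer that the same measure defines the Per Protocol set. The Secondary aim analysis section ties that analysis to violation of group allocation and does not mention adherence.

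Fifth, the fall from 11/15 to 11/20 = 55% is an extreme: it needs five discontinuers in one arm, all below the threshold, and completers at the bare minimum pass.

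Finally, feasibility is not among the formal aims, which limits the weight of the point. Counting mandated stops as failures is a choice of definition, not a correction.

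**Conclusion.** The point holds for the feasibility and acceptability conclusion only. The mismatch between an 80%-of-doses criterion and a question about one day a week is on the page. Under complete, truthful answers and independent days, it gives 25-38% false passes at a true 75% and 16-29% false failures at a true 85%. The net effect on the arm's rate depends on the spread of true adherence, which is unknown, so no direction is claimed for this part. If missed doses follow a weekly pattern, the error could differ from these figures.

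The exclusion of discontinuers does have a direction, upward, on two conditions: that it applies to the adherence rate, and that those removed were below 80%. With the one or two discontinuers that the article's own rates suggest, the smallest pass of 73.3% becomes 68.8% or 64.7%. A clearer pass, such as 13/15, would survive that many.

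The efficacy comparison and its power are not touched. The change is worth making because a fixed decision rule is attached to the measure and the unasked days cannot be recovered afterwards.

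**What to change.** 1. Reword the weekly REDCap item to ask how many of the last 7 capsules were taken, and calculate each participant's adherence from the sum over the capsules prescribed.
2. State that the feasibility proportion is calculated among everyone randomised to montelukast, including those who discontinue and are replaced. Count participants who leave before month 6 as not reaching the threshold, and report protocol-mandated stops separately so that they can be told apart from missed doses. Use the same denominator in the sentence with the 70% rule.
3. Say what the drug log records. A count of returned capsules is an optional cross-check. Blinded staff would collect the containers and hand them over, because the Blinding section allows the unblinded personnel who prepare treatments no other patient contact.

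The cost is one reworded question and a sentence or two of text, plus a hand-over step if capsules are counted. The downsides are slight recall error over 7 days and a feasibility rate that may be less favourable.

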#### Minimizing attrition

In order to maximize retention participants will be asked to provide alternate contacts and to specify whether study staff may leave messages or send mail. To promote attendance, patients will be contacted by phone both 1 week and 1 day prior to their study visits. In addition to ease the burden of attending subject visits they will be compensated for attending the follow-up study visits. The research coordinator and the PIs will track all study visits and will follow-up on any missed visits. Proactive strategies will be developed to work with participants who have trouble attending study visits. Participants will have 7:30 am–5 pm access to research personnel. In addition, while there are several study visits, all study visits can be scheduled to coincide with their physician follow-up appointments. We are currently employing these strategies in several ongoing trials and we have consistently resulted in less than 10% of ACL-reconstructed patients being lost to follow-up from our previous and ongoing clinical trials.

#### Confidentiality

Once enrolled, patients will be identified with a study ID in all study documentation, both written and in REDCap. Identifiable information (name, medical record number) will be kept separate from all study data and will be located on the password-protect excel spreadsheet on the secure department server behind the UK HealthCare firewall. The password will only be known by appropriate study personnel that are included in the approved IRB Study Personnel list. The identifiable information will not be transferred or collected in the data collection forms used for the study.

#### Data monitoring

Clinical site monitoring will be conducted by a member of the research team, [name], to ensure that the rights and well-being of trial participants are protected, that the reported trial data are accurate, complete, and verifiable, and that the conduct of the trial follows the currently approved protocol/amendment(s), with International Conference on Harmonisation Good Clinical Practice (ICH GCP), and with applicable regulatory requirement(s).

Remote clinical monitoring will be performed within 2 weeks following enrollment of the first subject, and repeated bi-annually (6 months) thereafter. Remote monitoring will include comprehensive, 100% data verification. Independent audits will not be conducted by the study sponsor to ensure monitoring practices are performed consistently across all participating sites as this is a single-site study.

[name] will conduct monitoring to verify that (a) the rights and well-being of human subjects are protected; (b) the reported trial data are accurate, complete, and verifiable from source documents; (c) the conduct of the trial is in compliance with the currently approved protocol/amendment(s), Food and Drug Administration (FDA) regulations and ICH guidelines; (d) ensure the quality and integrity of clinical study data; and (g) evaluate the progress of the study and ensure completion of the clinical study in a timely manner.

### Data collection

#### MRI analyses

All subjects will undergo MRI examination at visit 4 (1 month after ACL reconstruction) and visit 6 (12 months postoperatively). At one of the enrollment sites, the average time between initial presentation to the orthopedic surgeon and the date of surgery is 9 days. As such, it is often difficult logistically for patients and/or their caregivers to attend a study-specific MRI visit preoperatively when they have already had to take time away from school or work to have the clinical MRI performed in order to confirm the original injury diagnosis. Thus, we will rely on the clinical MRI and clinical exam to determine eligibility and have opted to have the baseline research protocol MRI images collected 1 month postoperatively as this is more feasible for patients and this timing is consistent with other groups studying cartilage changes after ACL reconstruction [56].

At both enrollment sites, sagittal and axial MRI images will be acquired using a 3.0-T MRI scanner and an 1Tx/15Rx phased array knee coil/flex coil. Sagittal and axial T1-weighted fast spin echo images (FSE) will be acquired to allow semiquantitative analysis at the conclusion of the study. These sequences will be followed by a sagittal high-resolution 3D dual echo steady state (DESS) sequence for cartilage segmentation and a sagittal combined T1ρ/T2 mapping for the quantification of cartilage composition. The major parameters for the DESS sequences are as follows: FOV = 140 mm, matrix = 384 × 307 × 176, resolution = 0.36 × 0.45 × 0.7 mm^3^, time of repetition (TR)/time of echo (TE) = 17.6 ms/6.0 ms. The T1ρ/T2 mapping will be acquired using a 3D MAPSS sequence with major parameters: FOV = 140 mm, image matrix = 320 × 160 × 24, resolution = 0.44 × 0.44 × 4 mm^3^, time of recovery = 1.5 s, bandwidth = 400 Hz/Pixel, TR/TE = 7 ms/3 ms, time of spin lock (TSLs) = 0, 10, 40, 80 ms for T1ρ mapping and preparation TEs = 0, 20, 40, 60 ms for T2 mapping. The scan time will be approximately 12 min for the combined T1ρ/T2 mapping. Images will be obtained with the knee in full extension.

Images collected at the University of Kentucky will then be transferred digitally to the University of California, San Francisco (UCSF) to be analyzed in the [name] Lab which is part of the Musculoskeletal and Quantitative Imaging Research Group (MQIR) at UCSF. Based on the high-resolution DESS images, articular cartilage will be segmented using a spline-based, semiautomatic technique. The T1ρ map will be created on a voxel-by-voxel basis using established fitting routines. The segmented masks will then be overlaid on the T1ρ maps after registration between DESS and T1ρ images, and mean T1ρ values will be calculated for the entire tibiofemoral cartilage, medial and lateral tibial plateau, medial and lateral femoral condyles, and the patellofemoral compartment will be calculated. Semiquantitative analyses will also be performed to assess abnormalities of the cartilage, meniscus, and bone marrow by an experienced musculoskeletal radiologist using the MRI Osteoarthritis Knee Score (MOAKS) [57].

In addition to assessing cartilage changes on MRI, we will also assess bone shape changes after ACL reconstruction. The bone area of the medial femoral condyle has been shown to increase within the first few months after ACL reconstruction [58, 59]. This is clinically meaningful as similar bony changes have been previously associated with progressive OA and within 6 months of ACL reconstruction correlated with subsequent patient-reported outcomes and MRI markers of cartilage quality at 3 years [58, 59]. [name] group at the Cleveland Clinic has previously established the methods to assess bone shape changes after ACL reconstruction [59]; images from both enrollment sites will be transferred digitally to the Cleveland Clinic for analysis.

#### Patient-reported outcomes

In addition to the aforementioned assessments of depressive symptoms with the PHQ-9 questionnaire, we will also be assessing knee-related patient-reported outcomes at the five clinic-based study visits using the Knee injury and Osteoarthritis Outcome Score (KOOS). The KOOS is comprised of 5 subscales (Pain, Symptoms, Activities of Daily Living, Sports and Recreation, and Quality of Life) with each scale being scored from 0 to 100 with higher scores being indicative of a superior outcome [60]. In addition, we will calculate the KOOSglobal score, which is a global score indicative of overall knee symptoms and function that has been validated in ACL reconstruction patients [61], as well as the patient acceptable symptom state (PASS) from the KOOS quality of life domain [14, 62].

At the 6- and 12-month follow-up visits, participants will also be asked to complete the single patient acceptable symptom state (PASS) question, which requires the participant to consider all aspects of life to determine if the state of the knee is “satisfactory” 1 year following surgery and postoperative treatment [63]. The specific phrasing of the PASS question will be, “Taking into account all the activity you have during your daily life, your level of pain, and also your activity limitations and participation restrictions, do you consider the current state of your knee satisfactory?” to which the participants will have the option to respond either “yes” or “no” [63].

#### Biomarker analyses

Blood and urine specimens will be collected on the day of surgery and all postoperative study visits to determine concentrations of the following biomarkers of inflammation, NFκB activation, cartilage degradation, and bone turnover. The selected urinary biomarkers have been shown to be predictive of inferior clinical outcomes and cartilage thinning [14, 64]. These validated biomarkers allow accurate assessment of cartilage degradation and bony remodeling and will be performed at the Duke Molecular Physiology Institute’s Biomarkers Shared Resource. In addition, both the involved and contralateral knees will be aspirated and synovial fluid collected on the day of surgery to assess inflammatory mediators and biomarkers of cartilage degradation. To avoid dry aspirations and missing data, the knee aspirations will be performed with a 5-mL saline lavage and normalized to urea content [65]. We anticipate that increased synovial fluid concentrations of a biomarker of proteoglycan loss (glycosaminoglycan (GAG)) and inflammatory mediators at the time of surgery would be predictive of increased MRI evidence of cartilage degradation postoperatively for the control group but would not be associated with increased cartilage changes in the montelukast group should that treatment be effective.

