### Participants

Participants will include 30 individuals undergoing primary ACL reconstruction (15 in the treatment group and 15 in the placebo group). Potential study participants will be identified by members of the research team during regularly scheduled office visits at the University of Kentucky’s Orthopaedic & Sports Medicine or University of California San Francisco Sports Medicine Center. After being identified as a potential study participant, the patient will meet with a member of the research team coordinator. Provided that the patient meets all inclusion and exclusion criteria, a member of the research team will begin the process to obtain informed consent. As part of the consent process, patients will have the option to allow the investigative team to store their data and biological specimens for future ancillary studies. We routinely recruit subjects from these physicians’ practices using similar methods.

In March, 2020, the FDA required a Boxed Warning about serious mental health side effects for montelukast which includes the risks of suicidal behavior and other serious neuropsychological events [30]. Children and adolescents will be excluded from the current trial as neuropsychological side effects of montelukast have been reported to be more common in children and adolescents than adults [31, 32]. To further avoid the potential for exacerbation of a pre-existing psychological condition, we will also exclude those with depressive symptoms and those that endorse suicidal ideation at the time of enrollment. Psychological screening and safety monitoring will be described in more detail below.

This trial will specifically target those that may be at greatest risk of a more rapid PTOA onset (age range 25–50 with concomitant meniscus injury as evidenced on their clinical preoperative MRI and clinical exam) [33–35]. Those who are undergoing revision procedures will be excluded; however, patients will not be excluded if they have had a previous contralateral ACL injury and/or surgery. In doing so, we hope to address the needs of the most at-risk patients but also those in whom a treatment signal could be feasibly detected.

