##### Cartilage remodeling

Following ACL injury, proteoglycan loss progresses as evidenced by a decrease in synovial fluid GAG [69]. This loss in proteoglycan content has been reported to be followed by a subsequent onset of collagen damage and an increase in the synovial fluid concentration of biomarkers of type II collagen breakdown (CTXII) with CTXII released into the synovial fluid and the circulation [69]. Urinary CTXII has been identified as a biomarker for the diagnosis, staging, and evaluation of the prognosis of hip and knee OA [70, 71] and has also been demonstrated to be responsive over short testing periods (3 months) [72]. We have reported that CTXII correlates with the degree of joint destruction and increases significantly within 1 month after ACL injury [4, 9]. In addition to markers of cartilage degradation, we will also assess a biomarker of type II collagen synthesis in the serum and synovial fluid (N-terminal propeptide of collagen IIA (PIIANP) as low-serum PIIANP has been predictive of clinically relevant progression of both OA symptoms and cartilage degradation [64].

Synovial fluid concentrations of GAG will be quantified using a commercial kit per the manufacturer’s instructions (Kamiya Biomedical Company, Seattle, WA, USA) as previously described [69]. CTXII will be measured in the urine by ELISA (Cartilaps® (CTX-II); Immunodiagnostic Systems, Inc, Fountain Hills, AZ) [4, 9] and will be normalized to creatinine levels (Quidel, San Diego, CA) [64, 73]. PIIANP will be measured in the serum and synovial fluid by ELISA (Merck Group/Millipore, EZPIIANP-53 K, [64]).

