#### Secondary aim analysis

Variables will be assessed for normality and if normally distributed, baseline and 1-year T1ρ and T2 relaxation times as well as bone shape changes will be compared between groups using a 2 × 2 repeated measures ANOVA (group × time). Based on previous work, it is expected that the biomarkers of type II cartilage breakdown (CTXII) and bony remodeling (CTXIα) will not be normally distributed and it is anticipated that biomarker concentrations will be transformed using Box-Cox transformation [66]. A 2 × 4 repeated measures ANOVA (group × time) will be used to assess changes in biomarker concentrations between the montelukast and placebo groups. The ordinal semiquantitative MOAKS data will be compared between groups using chi-square or Fisher exact tests as appropriate.

For both primary and secondary analyses, in the case of participants that violate group allocation, we will perform Intention-to-Treat and Per Protocol analyses. We will not employ imputation methods in the case of missing data. No interim or other subgroup analyses will be performed.

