#### Power analysis

The primary outcome variable is the change in medial femoral condyle T1ρ relaxation time on MRI between 1 and 12 months postoperatively. Based on a previous study of ACL-reconstructed patients, we assume a standard deviation of 2.86 ms [78]. With a sample size of 15 patients per group, the trial is 81.5% powered to detect differences of 3.09 ms between groups (effect size = 1.08). A difference of this magnitude is feasible when one considers the differences previously noted for ACL reconstructed knees with concomitant meniscus tears [78]. This sample size is feasible for this multicenter trial. In a review of all ACL-injured patients seen at the University of Kentucky in 2019 ([name], unpublished raw data), 50 patients that met the study inclusion and exclusion criteria were seen. We anticipate a similar volume at the University of California San Francisco thereby providing a recruitment pool of approximately 100 eligible patients per year.

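### The plan links montelukast's effectiveness to a synovial-marker association that is present in controls and absent on treatment, a contrast that does not show the arms differ with 15 per arm

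*Protocol article*

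**What the plan says.** The Protocol article, Biomarker analyses, describes aspirating both knees on the day of surgery and then states an expectation. It begins "We anticipate that increased synovial fluid concentrations of a biomarker of proteoglycan loss", adds inflammatory mediators, and says that these "would be predictive of increased MRI evidence of cartilage degradation postoperatively for the control group". For the treated arm it says that they "would not be associated with increased cartilage changes in the montelukast group should that treatment be effective".

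The Statistical analysis section does not return to this association. Primary aim analysis and Secondary aim analysis compare the arms by group-by-time repeated measures ANOVA, with chi-square or Fisher exact tests for MOAKS. Power analysis names the change in medial femoral condyle T1ρ as the primary outcome variable. Participants gives the arm sizes: "15 in the treatment group and 15 in the placebo group".

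On GAG itself, Cartilage remodeling says that after ACL injury "proteoglycan loss progresses as evidenced by a decrease in synovial fluid GAG".

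**The concern.** The expectation sets two arm-specific readings side by side and ties their contrast to whether the drug works. Finding an association in one group and failing to find it in another is not a comparison of the two. In a small arm, a real association is easily missed, so the anticipated picture can appear when the marker relates to cartilage change identically in both arms.

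The reasoning is also unsafe in the other direction. If the drug reduces degradation by the same amount at every marker level, it is effective and the association persists. A persisting association would then count wrongly against it.

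At stake is a mechanistic claim, that montelukast breaks the link between joint state at surgery and later cartilage loss, made on data that do not support it. The GAG wording adds to this. Without one stated direction, a correlation of either sign could be presented as agreeing with the plan.

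**Working it through.** **Inputs.** 15 per arm (Participants). SD of T1ρ change 2.86 ms and difference 3.09 ms (Power analysis). Alpha and sidedness are not stated, so two-sided 5% is assumed. No correlation between synovial markers and MRI change is given, so a range is used.

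**1. The plan's own figure.** The article says that "the trial is 81.5% powered to detect differences of 3.09 ms between groups (effect size = 1.08"). Effect size: 3.09 / 2.86 = 1.080. Noncentrality: 1.080 × √(15/2) = 2.96. A two-sample t-test with 28 df at two-sided 5% has power 81.49%. The stated 81.5% reproduces, which supports two-sided 5% as the working level. It concerns the difference in means only; the article gives no figure for the association.

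**2. What counts as an association in one arm.** With n = 15 there are 13 df and t = 2.160. The critical correlation is 2.160 / √(13 + 2.160²) = 0.514. A sample correlation below that would be read as no association.

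**3. How often the pattern appears with no difference between arms.** If both arms share the same true correlation r, and p is the chance of a significant positive result in one arm, the chance of significant in control but not in montelukast is p(1 − p). Simulation (200,000 trials per setting, bivariate normal, 15 per arm) gave:

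| True r in both arms | p | p(1 − p) | Simulated |
|---|---|---|---|
| 0 | 0.025 | 0.024 | 2.4% |
| 0.3 | 0.194 | 0.156 | 15.6% |
| 0.4 | 0.324 | 0.219 | 21.9% |
| 0.5 | 0.501 | 0.250 | 25.1% |
| 0.6 | 0.701 | 0.210 | 20.9% |

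Outside that range the rate falls: 9.5% at r = 0.2 and 10.7% at r = 0.7. For r from 0.2 to 0.7, only 9% to 19% of the trials showing the pattern also had a significant difference between the two correlations.

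**4. A direct comparison.** The Fisher z test of the difference between the two correlations rejected in 4.9% to 5.0% of the same simulated trials. A separate simulation of the regression interaction test (40,000 trials) gave 5.0% to 5.2%.

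**5. Power of the direct comparison.** For true correlations of 0.5 and 0: atanh(0.5) = 0.549, standard error √(1/12 + 1/12) = 0.408, ratio 1.346. Power is 1 − Φ(1.96 − 1.346) ≈ 27%; the opposite tail is negligible. The simulated regression interaction gave 26.5%. By the same formula power is 40% for 0.6 versus 0, 57% for 0.7 versus 0 and 77% for 0.8 versus 0. For 80% power at 0.5 versus 0, the size per arm is 2 × (1.960 + 0.842)² / 0.549² + 3, about 56.

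**6. An effective drug that leaves the association intact.** Let T1ρ change = a + b × marker − δ × group + error. With δ = 3.09 ms the drug achieves the full planned difference. The slope b and the within-arm correlation are the same in both arms, because subtracting a constant changes neither.

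**7. GAG.** Biomarker analyses expects higher synovial GAG to go with more later damage. Cartilage remodeling describes progressing proteoglycan loss as shown by falling synovial GAG. The article does not reconcile the two.

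**The case against.** The strongest reply is that the sentence is not an analysis rule. It opens as an anticipation, sits under Data collection, and runs from effectiveness to pattern, not from pattern to effectiveness. It names no test, no threshold and no separate within-arm analysis. It could be a plain-language description of a marker-by-group interaction, and the full protocol or an analysis plan may specify one. Much of this stands. A reader might infer that efficacy will be decided by this contrast; the article does not say so, and it assigns efficacy to the between-arm analyses. The absence of a named test is no finding either. What remains is the inference that is written down: present in one arm, absent in the other, tied to effectiveness. That inference is unsound in both directions, whatever test follows.

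The rates also depend on assumed correlations. That is right, and if a marker has no prognostic value the rate is only 2.4%. The sentence itself, however, expects the markers to be predictive in controls, so a correlation above zero is the case it has in view.

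On GAG, one statement compares patients on the day of surgery and the other describes change over time after injury, so they need not contradict each other. This too stands: it is a tension to clarify, not a proven error.

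**Conclusion.** The point holds in a limited form. The anticipated contrast is not evidence that the arms differ. With a shared true correlation of 0.3 to 0.6 it arises by chance in about 16% to 25% of trials per marker, against about 5% for a direct between-arm test. This rests on 15 complete patients per arm, bivariate normality, two-sided 5% and assumed correlations. The primary and secondary between-arm analyses are untouched.

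Two stronger readings are not supported:

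- A reader might see a conflict with the statement that "No interim or other subgroup analyses will be performed". Randomised arms are not subgroups of patients in that sense, so there is none.
- A reader might multiply the per-marker rate over GAG and the 13 listed mediators as if they were independent. Fourteen mutually uncorrelated markers cannot each correlate at 0.3 or more with one outcome, because 14 × 0.3² = 1.26 exceeds 1. The article also does not say that all of them will be screened. No multi-marker rate is claimed here.

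**What to change.** In Biomarker analyses, label the association exploratory and replace the present/absent contrast with one model per marker: T1ρ change on the day-of-surgery synovial marker, group, and marker-by-group. Base any statement about the drug on the interaction estimate and its 95% confidence interval. Add that a null interaction is not evidence of no modification, given the low power with 15 per arm, and that a persisting association does not show the drug to be ineffective. State one expected direction for synovial GAG and reconcile it with Cartilage remodeling.

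The cost is a few sentences and no new data. The drawback is that the evidence reported will look weaker than two separate correlations, with wide intervals.
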